#### RCT component

The primary study assessing patient outcomes (study components 3–6 described below) is an RCT, in which the two upgraded bedspaces are defined as intervention, while the 25 ‘conventional’ bedspaces serve as control. Eligibility screening, consent, and randomised allocation is a two-step process. All patients admitted to ICU are eligible to be randomised 1:1, except those deemed unsuitable for admission to the intervention bedspaces:

Patients requiring extracorporeal membrane oxygenation, intra-aortic balloon pump, or dialysisPatients admitted to ICU immediately following cardiac surgery, including transplantation

Patients will be randomly assigned to bedspaces as follows:

A random sequence of allocations to intervention and control bedspaces was established by the research coordinator and sealed in numbered, opaque envelopes. ICU floor coordinators and clinical personnel are blinded to this sequence until revealed at randomisation.Randomisation is completed by the ICU floor coordinator/admitting ICU doctor when:At least one intervention and one control bedspace are available at the time a patient is accepted for admission.The patient is eligible for randomisation (see above).The ICU floor coordinator or responsible clinician on duty opens the next envelope in sequence to reveal allocation of the patient to an intervention or control bedspace.The patient is assigned to the allocated bed.Patients will then be assessed for eligibility for participation in the study by a member of the research team (see ‘Recruitment’ section below).

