### Recruitment

For an estimated study period of 2 years, all patients randomised to an intervention or control ICU bedspace as part of the RCT or admitted to environmental control bedspaces as part of the case–control study will be screened for suitability to participate in the research study. Suitable patients will be approached by a member of the research team as soon as possible after admission to ICU, in consultation with the treating clinical team. As patient status commonly changes throughout ICU admission, patients may be screened daily until discharge and may be recruited to the study at any time during their admission to ICU if suitable based on the following inclusion/exclusion criteria:

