**Fig. 2 Fig2:**
[figure not shown]
Study schedule of enrolment, intervention, and assessments

Patients for whom consent is obtained will complete the study components listed below. Based on annual admission numbers and current admission diagnoses and presentations, the average number of patients eligible for randomisation per bedspace in the study facility is approximately 30 per year. We therefore estimate that approximately 250 patients will be randomised over 2 years. We expect that approximately 50 patients will be ineligible for participation for various reasons and based on other studies in the unit we have conservatively estimated a 50% patient decline rate. We therefore estimate that approximately 100 patients will provide consent and be recruited to this study over the 2-year study period.

A power calculation for this study is not possible, due to the lack of studies reporting the impact of environmental upgrades on patient outcomes. Therefore, an interim analysis will be conducted after 6 months of data collection, focussing on recruitment rate, completion rate for the various study components, and in-hospital outcome measures, with a power calculation performed based on this data to determine the number of participants required.

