### Data collection and monitoring, study components, and data analysis

Data describing participant demographics and ICU admission will be collected from hospital records and recorded on case report forms (CRFs). Data collected will include date of birth, gender, hospital and ICU length of stay, ICU and hospital survival, ICU readmission rates, mechanical ventilation time, details of their illness, medical treatment, and existing comorbidities. Completed CRFs will be entered into an electronic database. Patient characteristics and ICU admission data will be described using summary statistics. The number of patients approached and consented will be charted, together with the number who dropped out or died.

A data monitoring committee was not considered as this was a low-risk intervention. Data monitoring and study conduct is reviewed 6 monthly by the research investigators and submitted for ethics committee review yearly.

In addition to data from the study components being individually analysed and reported as described below, data analysis will also investigate the relationships between different outcomes/components. Inter-related components that will be explored include whether observed differences in sleep architecture is correlated with changes in delirium outcomes, and whether a difference in the maintenance of circadian rhythm between intervention and control bedspaces impacts the incidence of PICS at 6-month post-ICU discharge.

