#### Component 7: health economic evaluation

A within-trial cost-effectiveness analysis will be conducted to estimate the changes to total costs and patient outcomes associated with the intervention. The change to total costs will reflect the cost of implementing the intervention under different scenarios, offset by the economic value of ICU bed days saved from reduced ICU length of stay [43]. Planned scenarios will consider different definitions of implementation costs per intervention bedspace, which will impact the change in total costs per unit of health benefit. Definitions will reflect the cost of maintaining a bedspace that already exists in the ICU (base case), the cost of adding a new bedspace within an existing ICU, and the cost of building a new ICU to accommodate the intervention. These costs will be measured from the health system perspective. We will further consider the economic value of lost productivity from the patient perspective, which will be collected using the patient employment information questionnaire. Patient outcomes will be measured in quality-adjusted life years, which reflect patient life expectancy adjusted for health-related quality of life. Life years will be estimated using Australian life tables based on patients’ sex and age at the time of ICU admission. Quality of life, measured under component 6 via the EQ-5D-5L, will be used to estimate health utility values needed to convert life years to quality-adjusted life years.

Cost-effectiveness outcomes will be reported as an incremental cost-effectiveness ratio and net monetary benefit, for different willingness to pay thresholds. The impact of model input uncertainty on cost-effectiveness outcomes will be examined by deterministic sensitivity analysis and probabilistic sensitivity analysis. Model input distributions needed to conduct sensitivity analyses will be informed by available study data, published literature, and expert opinion where appropriate. Full details of analysis methods, assumptions, and results will be transparently reported in accordance with the 2022 Consolidated Health Economic Evaluation Reporting Standards (CHEERS 2022) checklist.

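### Component 7 prices ICU bed days saved, but length of stay is collected for participants, whose entry after allocation depends on their stay, so the estimate need not equal the saving per patient allocated to an upgraded bed

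*Protocol article*

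**What the plan says.** Component 7 states: "A within-trial cost-effectiveness analysis will be conducted to estimate the changes to total costs and patient outcomes". The change in total costs is the cost of implementing the bedspace, "offset by the economic value of ICU bed days saved from reduced ICU length of stay". No other offset is named from the health-system perspective. Productivity is treated as an addition: "We will further consider the economic value of lost productivity from the patient perspective".

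The population has to be pieced together from other sections of the protocol article:

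- **RCT component.** The envelope is opened and the patient is placed in the allocated bed. Only after that: "Patients will then be assessed for eligibility for participation in the study by a member of the research team".
- **Recruitment.** Patients may be screened daily until discharge and "may be recruited to the study at any time during their admission to ICU".
- **Inclusion and exclusion criteria.** The expected ICU stay must exceed 24 h. Deep or moderate sedation and agitation are among the reasons for exclusion.
- **Recruitment estimate (text after Fig. 2).** "Patients for whom consent is obtained will complete the study components listed below". About 250 patients are expected to be randomised and about 100 recruited.
- **Data collection and monitoring.** "Data describing participant demographics and ICU admission will be collected from hospital records", and "Data collected will include date of birth, gender, hospital and ICU length of stay".

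No section says that length of stay will be taken for everyone randomised, or that selection by stay will be allowed for.

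**The concern.** Randomisation makes the two groups comparable at allocation. The participants are a subset formed later, by a process that depends partly on how long the patient stays. A patient with a long stay has many screening days on which to become suitable and consent; a patient with a short stay has few or none. Length of stay is therefore both part of the entry condition and the quantity that Component 7 compares.

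An ICU deciding whether to upgrade gains or loses bed days for every patient placed in the bed, not only for those who stayed long enough to be recruited. If the participants' difference departs from the difference among all allocated patients, the error passes directly into the change in total costs, the incremental cost-effectiveness ratio and the net monetary benefit. Baseline adjustment does not remove selection on the outcome itself. The planned deterministic and probabilistic sensitivity analyses vary an input around its estimate, so they do not by themselves recentre a biased one.

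**Working it through.** **1. The article's own figures.** (250 − 50 ineligible) × (1 − 0.50 declining) = 100 recruited, which agrees with the text. So 250 − 100 = 150 of 250 randomised patients contribute no participant data. Declining need not depend on stay. The requirements to be expected to stay, to be recruitable and to be still present can.

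**2. How the bias arises.** Let L be the stay and π(L) the chance of being recruited given that stay. The mean stay among recruited patients is E[Lπ(L)] / E[π(L)], which exceeds the mean in all patients by C = Cov(L, π) / E[π]. Hence

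saving seen in participants = true saving + (C in control arm − C in intervention arm).

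The error vanishes when the two C terms are equal, as they are with no effect and equal recruitment. Otherwise it can take either sign.

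With a constant daily enrolment chance p, a patient discharged during day k+1 has π = 1 − (1 − p)^k. At p = 0.2 this is 1 − 0.8² = 0.36 for a stay of 2.5 days and 1 − 0.8¹⁰ = 0.89 for a stay of 10.5 days.

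**3. Size, first model.** The article gives no mean or spread of stay, no effect size and no speed of recruitment, so all of these are assumptions: control mean 5 days; p from 0.2 to 0.8 and equal in both arms; enrolled if the enrolment day precedes discharge; at least 1,000,000 simulated stays per arm; stays floored at 0.3 day under the fixed cut. Figures are days saved.

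| Effect on stay | Distribution of stay | True saving | Seen in participants |
|---|---|---|---|
| None | any | 0 | 0 |
| 20% proportional cut | log-normal, log-SD 0.8-1.0 | 1.0 | 0.90 to 1.15 |
| 20% proportional cut | exponential | 1.0 | 1.01 to 1.24 |
| 1 day off every stay | log-normal, log-SD 0.6 | 0.99 | 0.40 to 0.56 |
| 1 day off every stay | log-normal, log-SD 0.8 | 0.95 | −0.02 to 0.12 |
| 1 day off every stay | exponential | 0.84 | about 0 |
| 1 day off every stay | log-normal, log-SD 0.9 | 0.94 | −0.09 to −0.23 |
| 1 day off every stay | log-normal, log-SD 1.0 | 0.91 | −0.31 to −0.46 |
| 1 day off stays over 2 days only | log-normal | 0.66 to 0.88 | 0.28 to 0.81 |
| 1 day off stays over 4 days only | log-normal | 0.39 to 0.52 | 0.48 to 0.64 |

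For log-SD 0.8-1.0 and exponential stays, the mean control stay is itself overstated by about 8-61%.

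**4. Size, second model.** Assumptions: log-normal stays with median 1.5-3 days and log-SD 0.8 or 1.0; recruitment only after a stay of more than 1 day; exponential recruitment time at 0.5 or 1 per day.

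- 20% proportional cut, equal recruitment: participants show 77-100% of the true saving, with the right sign.
- 30% cut confined to stays under 2 or 3 days: true saving 0.10-0.32 day; participants show an apparent loss of 0.16-0.50 day in all 12 settings.
- No effect, but one arm recruited twice as fast: a spurious difference of 0.24-0.58 day, in either direction.

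**5. Precision.** If the variance of stay were the same in both populations, using 250 rather than 100 patients would multiply the standard error by √(100/250) = 0.63, a reduction of about 37%.

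**The case against.** The strongest objection is that Component 7 never names the population for bed days saved. It allows model input distributions to draw on literature and expert opinion as well as study data, and the full protocol exists separately and may settle the matter. This stands as a limit: the participants-only reading is an inference from the within-trial label together with the recruitment and data-collection sections. It is nevertheless the natural reading, because those sections fix who contributes data and nothing points to another source of stay.

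A reader might go further and infer that the estimated saving will be badly wrong or reversed in sign. The documents do not support that. With equal recruitment, reversal needs particular effect shapes, such as a whole day off every stay with widely spread stays, or an effect confined to short stays. Under a proportional cut the error is modest, and under some shapes the saving is overstated.

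Nor does it follow that the patients who benefit most leave before they can be enrolled. Under a proportional effect the longest stays save the most days, and those patients are the likeliest to be recruited.

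It can also be said that the 24-hour criterion simply defines a narrower target population. That is partly right, but the criterion is judged after allocation, and presence in ICU at recruitment is a further condition that the bedspace could influence. Recruitment speed could also differ by arm, because the bedspace is visible and sedation and agitation are assessed once the patient is in it. Whether it will differ is unknown.

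**Conclusion.** The concern holds in a limited form. As the article reads, the bed-days term compares groups selected after randomisation by a process that depends on the outcome being priced. The result therefore need not equal the saving per patient allocated to the bed.

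Under the assumed 5-day control mean and equal enrolment, the error is at most about a quarter of the true saving for a 20% proportional cut (0.90-1.24 against 1.0 day). For a fixed 1-day cut to every stay it ranges from losing roughly half the saving to reversing its sign, depending on the spread of stays. It is nil when there is no effect and recruitment is equal. A spurious difference can appear when recruitment speed differs by arm. The article supplies none of the inputs needed to say which case applies.

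This should be corrected, because it bears on the one cost offset the evaluation names and the remedy is inexpensive. It does not affect the utility side of Component 7 in the way shown here.

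**What to change.** State the length-of-stay population in Component 7. For the bed-days term, use ICU length of stay by allocated arm for all randomised patients (about 250), taken from routine admission and discharge times and linked to the envelope log, in non-identifiable form. Keep utilities from consenting participants, and report participants-only stay as a secondary figure.

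The cost is an ethics amendment and a small data extract, with no patient contact. Approval cannot be taken for granted, because the extract would include patients who declined or were ineligible.

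If approval is refused, analyse stay with delayed entry at the enrolment date and limit the stated saving to patients still in ICU at recruitment. This is a weaker substitute, since it does not restore the comparison as randomised. The gain in precision (standard error about 37% lower) should be claimed only with the equal-variance assumption stated.

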## Discussion

Despite emerging evidence of the negative impact the physical and sensory ICU environment can have on patient recovery, this is an area of critical care medicine that is commonly neglected during design of ICUs and development of patient care plans. ICU care plans usually involve setting targets, which may be targets for optimal sedation levels, ventilation settings, or amount of active exercise, but other factors essential for healing and recovery are commonly neglected, such as targets for quality and quantity of sleep overnight.

Similarly, while ICU clinicians prescribe treatments personalised to patient needs, the ICU environment is inflexible and not adapted to individual needs which necessarily change as the patient’s condition changes. With a growing evidence base demonstrating the importance of environmental factors such as natural light (or light that mimic natural light), noise reduction, biophilia (views of/access to nature), music therapy, and family support, and the rapid development of technology, there is now an opportunity to ensure that ICU bedspaces are flexible and dynamic, allowing personalisation of the space and the ability to modify the environment to suit the patient’s needs at the time. The environment can be optimised for individual patients and adjusted to aid recovery and help facilitate healing.

Previous research on environmental factors commonly addresses the outcome rather than the actual problems. For instance, studies have demonstrated that ear plugs and eye masks can help improve sleep in the ICU [44, 45]. However, this is masking rather than addressing the real problem, which is the continuous increase in noise levels in ICU, reported to increase linearly by approximately 0.4 dBA per annum [19]. Current evidence on the impact of environmental change on patient outcome is limited but suggesting that it may produce positive outcomes [29, 46–48].

The ICU of the Future project is aiming to address the commonly reported environmental problems in ICU. The protocol described in this manuscript employs mixed method methodologies to evaluate the impact of a quieter ICU with improved access to natural/circadian light, views of nature, and improved patient engagement on patient experience and outcomes. At the end of the evaluation, this study will provide new information on how an improved ICU environment can impact on patient short- and medium-term recovery, with a rigorous evaluation of multiple patient outcomes, including qualitative interviews to ensure the study also collects outcomes important to patients and their families. Importantly, a health economic evaluation will be completed, to evaluate whether the extra building and technology costs associated with upgrading the bedspace environment is offset by improved efficiencies and outcomes. An investment in getting the environment right has the potential for large, long-term positive impacts on both patient outcomes and staff health and performance, therefore producing better outcomes and cost savings. Given the significant proportion of hospital budgets invested into human resources, environmental modifications that reduce burnout and staff turnover even in small ways could quickly become cost-effective.

To our knowledge, this is the first study to investigate the impact of large environmental upgrades on patient outcomes in the ICU setting. The strengths of this protocol include the rigorous and multi-dimensional evaluation of both patient outcomes and experiences. The group of consumers (former ICU patients and their families) that helped co-design the upgraded ICU bedspaces also provided feedback and essential input into how they felt the bedspaces should be evaluated and therefore the study design, ensuring we are evaluating what is important to ICU patients. Limitations include that the study is conducted at a single site with a specific local context, potentially impacting on generalisability of data. Also, as only two bedspaces have been upgraded, the small number of beds will limit the number of patients we are able to recruit to the study. A prolonged data collection period, with regular interim data analyses, has been chosen for this reason to ensure sufficient data is collected to be able to compare the intervention bedspaces with control bedspaces. Additionally, there were no perfectly matched beds for the case–control sub-study. When the doors are closed, the implementation bedspaces function like a single room; however, the doors are much wider than the other single rooms in the unit making them functionally closer to open-plan bedspaces when the doors are open. Considering all the other single rooms have windows, it was therefore decided that the bedspaces closest in function and design to the implementation bedspaces were the three chosen open-plan and windowless ones. Lastly, during the upgrade of the two bedspaces, there were multiple changes made to the design, function, and technology in the bedspaces. Should the upgraded bedspaces demonstrate improved patient outcomes, it will not be possible to determine which feature(s) of the intervention bedspaces that contribute to these improvements, or their proportion towards contribution.

## Data Availability

The datasets analysed during the current study and statistical code are available from the corresponding author on reasonable request, as is the full protocol.

## Abbreviations

CRF: Case report forms
EEG: Electroencephalogram
EMG: Electromyogram
ICU: Intensive care units
PICS: Post-intensive care syndrome
PSG: Polysomnography
RCT: Randomised controlled trial
